### Randomisation and blinding

Allocation sequence is produced by a third party (pharmacologists at Glostrup Pharmacy, Glostrup, Denmark) using computer generation fixed block size with stratification by centre. Allocation concealment is secured by using sealed opaque numbered envelopes specially prepared for this trial and this unique number is used as patient trial ID. Participants, outcome assessors, trials investigators, statisticians and GCP trial monitors are blinded, as well as care providers such as midwives, obstetricians, anaesthesiologists and anaesthetist nurses. Anaesthetic personnel not involved in patient care randomise the patient and dispense the trial medicine. Two 50 ml opaque syringes (yellow coloured) will be delivered to the operating theatre without revealing the allocation. We register the success of blinding by asking the responsible team/physician in the operating theatre following administration if he or she has any hint of the allocated treatment and if yes, why. The patient is asked during the follow-up period.

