### Setting, location and follow-up

Parturients will be included during a two-year period at the four largest hospitals in the Capital Region, Denmark. These four centres are university-affiliated public tertiary care hospitals in the Copenhagen area each with 3500 to 7000 deliveries per year. Parturients are invited to participate at the pre-anaesthetic evaluation and will be hospitalised for at least 24 hours following inclusion. Participants are contacted by phone six weeks after the intervention, and they are able to contact the principal investigator during the full trial period. Blood transfusion and the use of tranexamic acid and other haemostatic agents follow Danish standard recommendations in all four centres and adherence to guidelines will be monitored as part of the conduction of this trial.

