### Outcomes and safety measures

The primary outcome is the need for transfusion with allogenic blood products. Secondary outcomes will be development of ‘severe PPH’ defined as: ‘decrease of haemoglobin (Hb) of > 4 g/dl (2.5 mmol/L), transfusion of at least four red blood cell (RBC) units, haemostatic intervention (angiographic embolization, surgical arterial ligation or hysterectomy) or death. We also evaluate estimated blood loss, total amount of blood transfused, the development of re-bleeding and Hb < 5.8 g/dL (3.6 mmol/L)’. We will register potential side effects such as: fever, headache, nausea, vomiting, allergic reactions, anaphylaxis and thromboembolic complications (deep venous thrombosis, acute myocardial infarction and pulmonary embolism) [40]. All suspected unexpected serious adverse reactions will also be reported in accordance with the International Conference on Harmonisation (ICH) GCP and the Danish Medicines Agency guidelines.

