### Statistical methods and data analysis

The two groups will be compared using chi-square test (binominal data) or Fischer’s exact test if numbers of expected values are less than five (or an unconditional exact test). Fibrinogen concentrate can potentially reverse the impaired haemostasis observed when using colloids [25,45]. The potential effect of fibrinogen concentrate may rely on the pre-administered use of colloids, so sensitivity analysis and the influence of this will be assessed together with other possible confounders (baseline variables/parameters are presented in Table 1). In accordance with ICH GCP recommendations on statistical principles for clinical trials (E9) [46], we will present adjusted and unadjusted analyses of the possible effect. The baseline variables/parameters will be assessed using multiple logistic regression models. The evaluation of pre-specified subgroups demands more participants than planned in this trial, however, to explore and guide further trials in this area we will perform two subgroups analysis: one on mode of delivery (vaginal versus caesarean section) and one on parturients with hypofibrinogenaemia at intervention, thus guiding upcoming trials in their selection of study population. All outcomes will be reported as ‘intention-to-treat’ analysis including all randomised patients fulfilling inclusion criteria and not meeting exclusion criteria with a standing consent to participate. Patients with the following major protocol violations will not be included in a supplemental per-protocol analysis: not receiving total dose and lack of follow-up. The impact of blinding level will be explored in a separate sensitivity analysis. Statistics will be performed before the code of allocation is revealed. If the overall level of missing data is less than 5%, we will perform complete case analysis. If more than 5% of missing data is the case, we will present ‘worst-case’ and ‘best-case’ analyses and if those are inconclusive, we will perform multiple imputations [47].

**Table 1 T1:** List of baseline parameters/variables to be assessed for baseline imbalance between treatment groups in the final analysis

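### Centre stratifies the randomisation but is in neither the planned test nor the Table 1 covariates; if transfusion rates differ by centre, the pooled test is conservative and loses a little power

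*Protocol article*

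**What the plan says.** Under Randomisation and blinding, the allocation list uses "computer generation fixed block size with stratification by centre". Setting, location and follow-up names four hospitals.

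Under Outcomes and safety measures, "The primary outcome is the need for transfusion with allogenic blood products", a yes/no endpoint. Statistical methods and data analysis then states: "The two groups will be compared using chi-square test (binominal data", with Fisher's exact or an unconditional exact test when expected counts are small. None of these is stratified.

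The same section promises that "we will present adjusted and unadjusted analyses of the possible effect", using multiple logistic regression. The candidate variables are given as "other possible confounders (baseline variables/parameters are presented in Table 1". That table is captioned "List of baseline parameters/variables to be assessed for baseline imbalance between treatment groups in the final analysis". It has 16 entries, among them mode of delivery, post vaginal procedure, blood loss before intervention and method of anaesthesia. Centre is not one of them, and no other part of the article names a centre-stratified or centre-adjusted analysis.

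**The concern.** Blocking within centre forces the arms to be nearly equal in size in every hospital. Differences between hospitals in the transfusion rate therefore drop out of the treatment contrast. A pooled chi-square still counts those differences in its variance. If they exist, the standard error is too large, the confidence interval too wide and the true type I error below the stated 5%, and power is lost that the design had already secured.

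The article is specific on both counts, naming the test and itemising the covariates, and the one factor built into the randomisation appears in neither. As written, the unadjusted and the adjusted analysis both leave it out.

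**Working it through.** **1. The plan's own figure.** Number of participants gives 107 per group for a 33% reduction, α = 0.05 and power 80%, but no control-group transfusion rate, so 107 cannot be rebuilt directly. Solving backwards, two-sided and without continuity correction:

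n = [1.96·√(2p̄(1−p̄)) + 0.842·√(p₁(1−p₁) + p₂(1−p₂))]² / (p₁−p₂)²

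With p₁ = 0.578 and p₂ = 0.67 × 0.578 = 0.387, p̄ = 0.483 and n = (1.385 + 0.584)² / 0.191² ≈ 107. A one-third reduction gives p₁ of about 57%. I use about 57% as an assumed mean control risk. It is not a figure in the documents.

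**2. Size of the pooled test.** Let r be the mean within-centre p(1−p) divided by the overall p̄(1−p̄). Under the null, with blocking and equal centres, the true size of a nominal 5% test is approximately 2·[1 − Φ(1.96/√r)].

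- All centres 57%: r = 1, size 5.0%.
- 45/53/62/70%: r = 0.2356/0.2444 = 0.964, size 4.6%.
- 35/50/65/78%: r = 0.2192/0.2451 = 0.894, size 3.8%.

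Because r cannot exceed 1, ignoring the strata can only move the size downwards.

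**3. Simulation.** 214 patients, four near-equal centres, blocks of four (block size assumed), risk ratio 0.67 for power, uncorrected chi-square against CMH by centre, 400,000 trials per scenario:

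| Assumed control risks by centre | Type I error, pooled / CMH | Power, pooled / CMH |
|---|---|---|
| 57% in all | 4.8% / 4.8% | 78.5% / 78.6% |
| 45/53/62/70% (span 25 points) | 4.4% / 4.9% | 79.3% / 80.3% |
| 35/50/65/78% (span 43 points) | 3.7% / 5.0% | 79.3% / 82.1% |

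Simulations with exact balance within centre gave the same pattern: pooled type I error 4.3% and a gain of 0.7 to 0.8 points for the middle row, 3.5% and 3.1 points for the last.

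**4. Other assumptions.** With a mean control risk of 25% and 214 patients, power moves from 31.8% to 32.2% for centre risks of 15–35%, and from 31.0% to 34.3% for 5–45%. Low power there reflects the lower event rate; the CMH gain is of the same order.

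**5. Cost when centres do not differ.** At the full 245 with 57% everywhere, power was 85.2% pooled against 84.9% CMH. With unequal centres of 35/50/70/90 patients it was 85.3% against 84.8%, the largest loss seen (about 0.4 points before rounding). The pooled test's simulated size in these cases was 5.3%, which comes from the discreteness of the counts and not from the stratification.

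**The case against.** The strongest reply is that the pooled chi-square is valid, that its error is on the safe side, and that the loss may be nil. The document supports much of this. The hospitals lie in one region ("These four centres are university-affiliated public tertiary care hospitals in the Copenhagen area each with 3500 to 7000 deliveries per year"), and transfusion and haemostatic agents "follow Danish standard recommendations in all four centres and adherence to guidelines will be monitored". That argues for modest centre differences and makes a 43-point span an extreme case. It does not exclude differences in case mix or in adherence, and the plan to monitor adherence suggests uniform practice is not taken for granted.

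A second reply is that Table 1 is captioned as a list for checking imbalance, where a factor balanced by blocking would naturally be absent. This stands only in part, because the text also uses the table as its list of possible confounders for the regression.

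A third is that an analysis plan, not shown, may add centre. It may. But the article itself fixes the test and the covariate list, and neither mentions centre.

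Three stronger readings are tempting and not supported:

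- **The 5% error rate is wrong as a matter of fact, or false positives become more likely.** Miscalibration from ignored strata arises only if rates differ by centre, for which there are no figures, and its direction is conservative.
- **The loss is substantial.** For a 25-point span it is 1 point of power or less.
- **Entry route, with its different blood-loss thresholds, is also ignored.** Table 1 already carries mode of delivery, post vaginal procedure and prior blood loss, and a subgroup analysis by mode of delivery is planned.

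**Conclusion.** The mismatch is real: centre governs the randomisation and is in no stated analysis. Its consequence is conditional and modest. If the four centres have the same transfusion rate, nothing is lost. If control risks span about 25 points, the pooled test runs at about 4.3–4.4% and gives up 0.7 to 1.0 point of power. At about 43 points it runs at 3.5–3.7% and gives up about 3 points. These figures assume 214 analysed patients, four near-equal centres, a mean control risk of about 57% obtained by back-solving, and a risk ratio of 0.67. The results would be somewhat too cautious, not invalid. The point merits correction because the remedy costs almost nothing, not because the planned test is unsafe.

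**What to change.** Make the primary test a CMH test stratified by centre, and report a centre-stratified risk ratio or risk difference with its 95% CI. Add centre to the adjusted logistic models. Keep the pooled chi-square as a supportive analysis. Entry route needs no change.

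This is a change of wording only: centre is known for every patient from the randomisation, so no data need to be added. If centres prove alike, the price is at most about 0.4 points of power. Trial Status reports 102 women included of the planned 245, and statisticians are blinded, so at that stage the change could be made without knowledge of results by arm.

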**Methods/Design:**

In this randomised placebo-controlled double-blind multicentre trial, parturients with primary PPH are eligible following vaginal delivery in case of: manual removal of placenta (blood loss ≥ 500 ml) or manual exploration of the uterus after the birth of placenta (blood loss ≥ 1000 ml). Caesarean sections are also eligible in case of perioperative blood loss ≥ 1000 ml. The exclusion criteria are known inherited haemostatic deficiencies, prepartum treatment with antithrombotics, pre-pregnancy weight <45 kg or refusal to receive blood transfusion. Following informed consent, patients are randomly allocated to either early treatment with 2 g fibrinogen concentrate or 100 ml isotonic saline (placebo). Haemostatic monitoring with standard laboratory coagulation tests and thromboelastography (TEG, functional fibrinogen and Rapid TEG) is performed during the initial 24 hours.

Primary outcome is the need for blood transfusion. To investigate a 33% reduction in the need for blood transfusion, a total of 245 patients will be included. Four university-affiliated public tertiary care hospitals will include patients during a two-year period. Adverse events including thrombosis are assessed in accordance with International Conference on Harmonisation (ICH) good clinical practice (GCP).

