### Inclusion criteria

Inclusion is possible if the following eligibility criteria are met: 1) Informed consent from participant. 2) Age ≥ 18 years. 3) PPH defined as bleeding from uterus and/or the birth canal within 24 hours postpartum. 4) Vaginal delivery and in need of anaesthesiological assistance and either: a) estimated blood loss exceeding 500 ml and intended manual removal of placenta; or b) estimated blood loss exceeding 1000 ml and intended manual exploration of the uterus due to continuous bleeding after the birth of placenta. 5) In case of birth by caesarean section and estimated perioperative blood loss exceeding 1000 ml (Figure 1).

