### Monitoring and data collection

Adherence to ICH GCP, including the Helsinki Declaration, and trial protocol is being monitored by independent monitors from the GCP unit at Copenhagen University, and data are being collected on paper case report forms. Transfusion data are assessed through multiple data sources including the Capital Region Blood Banks blood product registration system in which all used blood products are registered together with the recipient patients’ unique personal identification (cpr) number. This ensures an almost complete follow-up excluding only patients withdrawing consent to participate.

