### Number of participants

Approximately 1% of parturients receive blood transfusion [7,9,32,41-44] and 1.75% develop PPH (blood loss >1000 ml) [4]. No studies conducted in the obstetric target population were available during the design phase of this trial, however, the two available RCTs found a respectively 60% [25] and 20% but insignificant [26] risk reduction in the need for allogenic blood transfusions. Thus, we settled to investigate a risk reduction of 33%: with α = 0.05 and power (β) = 80%, a number of 107 patients in each group are needed in order to evaluate a 33% reduction in the need for blood transfusion. With a margin for missing data and dropouts of 15% - a total of 245 patients will be included.

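### The set called intention-to-treat is a modified ITT set, and it removes the withdrawn women whom the best-/worst-case analyses of the primary outcome should cover

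*Protocol article*

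**What the plan says.** Three statements in the protocol article bear on this point.

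- **Analysis set** (Statistical methods and data analysis). Every outcome is to be reported by intention to treat, on a set described as "including all randomised patients fulfilling inclusion criteria and not meeting exclusion criteria with a standing consent to participate". The only other set named is a supplementary per-protocol set, which is narrower still.
- **Source of the primary outcome** (Monitoring and data collection). Transfusion data come from several sources, including the regional blood-bank register linked by personal identification number. The article adds: "This ensures an almost complete follow-up excluding only patients withdrawing consent to participate".
- **Missing-data rule** (Statistical methods and data analysis). "If the overall level of missing data is less than 5%, we will perform complete case analysis". Above that level the rule changes: "If more than 5% of missing data is the case, we will present" worst-case and best-case analyses, followed by multiple imputation if these are inconclusive.

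The section Number of participants allows 15% for dropout and missing data, which takes 107 per group to a total of 245.

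**The concern.** An intention-to-treat analysis keeps every randomised woman in the arm to which she was allocated. The set described here does not. It applies two filters after randomisation, eligibility and standing consent, and the article names no analysis that puts these women back, not even as a sensitivity analysis.

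The consent filter matters more, because withdrawal happens after allocation and could be related to how the bleeding went. By the article's own account it is also the only reason for transfusion data to be lost. The definition of the set therefore takes out the women for whom best-/worst-case analysis exists. The trial could report a complete primary outcome under an ITT label, and the reader would see no bound for the women who left.

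**Working it through.** **1. Reading the passages together.** A woman who stays in the trial has register data on transfusion. A woman who withdraws does not, and she is also outside the analysis set. Expected missingness of the primary outcome inside the set is therefore about 0%, however many withdraw. If the 5% threshold is crossed through other variables, the best- and worst-case results for transfusion nearly coincide with the observed result, because there is almost nothing to fill in.

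The eligibility filter is separate. Ineligible women would have register data, so dropping them departs from ITT but does not affect the missing-data rule.

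**2. The plan's own figures.** The plan states "with α = 0.05 and power (β) = 80%, a number of 107 patients in each group are needed".

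- 2 × 107 = 214.
- 214 × 1.15 = 246.1, and 214 / 0.85 = 251.8. The stated 245 is close to the first.
- Margin actually built in: 245 − 214 = 31 women, and 31 / 245 = 12.7%.

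The article gives no transfusion rate for the control arm, so 107 cannot be derived directly. Taking α as two-sided (the article does not say) with 80% power, 107 per group results from 60% versus 40% with continuity correction. Without the correction, it results from a control rate of about 57.8% with a 33% relative reduction. The 60% versus 40% used below is therefore an assumption, and a range is shown.

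**3. What the bounds would show.** Let n = 245 / 2 = 122.5 per arm and m = women per arm with no usable outcome, taken as equal in both arms. Then k = n − m are retained, with events e₁ = k·p₁ (placebo) and e₂ = k·p₂ (fibrinogen).

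- Worst case: RR = (e₂ + m) / e₁
- Best case: RR = e₂ / (e₁ + m)

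Example with p₁ = 0.60, p₂ = 0.40, m = 15.5:

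- k = 107, e₁ = 64.2, e₂ = 42.8.
- Worst: (42.8 + 15.5) / 64.2 = 58.3 / 64.2 = 0.908.
- Best: 42.8 / (64.2 + 15.5) = 42.8 / 79.7 = 0.537.

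The p-values are from the chi-square test without continuity correction.

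| Assumed rates, placebo vs active | m per arm | RR in retained (p) | Best-case RR | Worst-case RR (p) |
|---|---|---|---|---|
| 60% vs 40% | 2.5 (2%) | 0.667 (0.002) | 0.644 | 0.701 (0.006) |
| 60% vs 40% | 6.125 (5%) | 0.667 (0.002) | 0.613 | 0.754 (0.028) |
| 60% vs 40% | 15.5 (12.7%) | 0.667 (0.003) | 0.537 | 0.908 (0.45) |
| 50% vs 33.5% | 6.125 (5%) | 0.670 (0.011) | 0.606 | 0.775 (0.09) |
| 50% vs 33.5% | 15.5 (12.7%) | 0.670 (0.014) | 0.519 | 0.960 (0.78) |
| 30% vs 20.1% | 15.5 (12.7%) | 0.670 (0.095) | 0.452 | 1.153 (0.49) |

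In the last row the retained women alone do not give p < 0.05, so withdrawal is not the cause of that result being inconclusive.

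**The case against.** The strongest reply is that bias should be limited. The eligibility criteria are facts that exist before randomisation: age, inherited deficiency, prepartum antithrombotics, pre-pregnancy weight, refusal of transfusion, blood loss at inclusion and the intended procedure. Allocation cannot change them. Investigators, outcome assessors, statisticians and monitors are blinded, and the analysis is done while the allocation is still masked. This largely stands, and it makes the loss of ineligible women mainly a matter of labelling and precision. Two limits remain. The text does not tie eligibility exclusions to blinded review of pre-randomisation facts, and blinding does not bring withdrawn women back into the comparison.

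It may also be said that data cannot be used once consent is withdrawn. That may be so, but the women can still be counted by arm as missing and bounded without using their data.

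Three stronger readings may tempt a reader, and the article does not support them.

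- *The complete-case branch always applies.* It need not. The trigger is the overall level of missing data. Laboratory values at four time points, secondary outcomes and the Table 1 covariates can all be missing and take that level above 5%. Follow-up is also described as almost complete, so a stray register gap is possible.
- *About 15% of women will be excluded, enough to create a false benefit.* The 15% is a planning allowance for dropout and missing data together, not a forecast of withdrawals, and the margin actually built in is 12.7%. A false benefit needs removals related differently to outcome in the two arms, and nothing in the article points to that.
- *The blood-loss cut-off lets women be dropped after the event.* The abstract puts the threshold at or above the stated volume ("Caesarean sections are also eligible in case of perioperative blood loss" of at least 1000 ml). The Inclusion criteria use a strict form ("estimated blood loss exceeding 1000 ml and intended manual exploration of the uterus"). The difference is minor, and no text describes women at exactly the cut-off being removed later. It adds nothing to this point.

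**Conclusion.** The point holds. The set labelled intention-to-treat is a modified ITT set, no analysis of all randomised women is named, and the best-/worst-case analyses would have essentially nothing to act on for the primary outcome. The main concern is withdrawal of consent; dropping ineligible women is a secondary departure with limited scope for bias.

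The size depends on the number of withdrawals, which the article does not predict. At 2% or 5% excluded, with 60% versus 40% assumed, the worst case still favours fibrinogen with p below 0.05. At an assumed control rate of 50%, 5% is already enough to take the worst case to p about 0.09. If the whole 31-woman margin were withdrawals, the worst-case risk ratio would lie between 0.91 and 1.15 for control rates from 60% down to 30%, and would not be significant at any of the rates examined. These figures assume equal losses in the two arms and a 33% relative reduction among the retained women. They show what the bounds could hide, not what bias to expect.

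**What to change.** Change the analysis wording before unblinding:

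- Make the primary set all randomised women, analysed as allocated, including those later found ineligible.
- For women who withdraw, use data up to withdrawal where consent allows. Otherwise count them by arm as missing.
- Report best- and worst-case bounds for the primary outcome among all randomised women, whether or not the 5% trigger is reached.
- Rename the present set 'modified ITT' and keep it as a sensitivity analysis. State that eligibility exclusions are decided blind on pre-randomisation facts, and report them by arm with reasons.

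The sample size does not change for this point. The cost is slight dilution from a few ineligible women, and a visible bound where women have withdrawn.

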### Objective

The aim of this study is to evaluate whether initial treatment with fibrinogen concentrate reduces the need for allogenic blood transfusion in postpartum haemorrhage (PPH). Other potential benefits and harms will be assessed as secondary outcomes.

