## Methods and design

### Overview

We are conducting a multicentre parallel placebo-controlled randomised double-blind clinical trial with 1:1 allocation ratio. The trial is investigator initiated and controlled and good clinical practice (GCP) monitored.

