### Exclusion criteria

Participants fulfilling one or more of the following criteria will be excluded: 1) Known inherited deficiencies of coagulation. 2) Anti-thrombotic treatment prepartum due to increased risk of thrombosis. 3) Pre-pregnancy weight <45 kg. 4) Refusal to receive blood transfusion.

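### As written, harms are compared only among eligible women with standing consent, so a dosed woman later found ineligible drops out of the thrombosis comparison

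*Protocol article*

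**What the plan says.** Three places in the protocol article bear on this point.

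- **Objective:** "Other potential benefits and harms will be assessed as secondary outcomes". The article thus classes harms as outcomes.
- **Statistical methods and data analysis:** "All outcomes will be reported as ‘intention-to-treat’ analysis", and the set is then defined as "including all randomised patients fulfilling inclusion criteria and not meeting exclusion criteria with a standing consent to participate". The only other set named is a narrower one. Women with either of two major violations "will not be included in a supplemental per-protocol analysis: not receiving total dose and lack of follow-up".
- **Exclusion criteria:** the second criterion is "Anti-thrombotic treatment prepartum due to increased risk of thrombosis".

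The section on outcomes and safety measures lists the side effects to be registered. They include "thromboembolic complications (deep venous thrombosis, acute myocardial infarction and pulmonary embolism"), allergic reactions and anaphylaxis. It adds a case-level duty: "All suspected unexpected serious adverse reactions will also be reported in accordance with" ICH GCP and the national agency's guidelines. It gives no separate analysis population for side effects.

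**The concern.** A comparison of harms normally counts everyone exposed to the product, because a side effect in a woman who should not have been enrolled is still a side effect of the infusion. The set defined here requires eligibility and continuing consent, and it applies to all outcomes. One of the exclusion criteria is itself a marker of thrombosis risk, so a dosed woman who fails that criterion leaves the comparison in which her outcome is most relevant.

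The article's Discussion names thrombosis as the possible downside of raising fibrinogen above normal levels in these patients, and its abstract says the trial is meant to support recommendations on early use. The thrombosis comparison will therefore be read closely, and it will rest on very few events.

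**Working it through.** **Which women are counted for harms**

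1. Harms are secondary outcomes (Objective).
2. All outcomes are analysed in randomised women who meet every inclusion criterion, meet no exclusion criterion and have not withdrawn consent (Statistical methods).
3. From 1 and 2, harms are analysed in that set. Neither section makes an exception.
4. Take a woman who received the infusion and is later found to have had prepartum antithrombotic treatment for thrombosis risk. She meets an exclusion criterion, so by 2 she is outside the set.
5. The supplemental per-protocol analysis does not bring her back. It only removes further women, namely those without the full dose or without follow-up.
6. Her event is still recorded as a side effect and, if it qualifies, reported as a suspected unexpected serious adverse reaction. She is lost from the between-group comparison only.

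**What one lost event does**

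The article gives no figure on this point to reproduce. The inputs are the planned total of 245 (Number of participants) and a "double-blind clinical trial with 1:1 allocation ratio" (Overview). 245 / 2 = 122.5, so one arm has 123 women and the other 122. The event counts below are assumptions.

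Limits are exact (Clopper-Pearson), two-sided 95%, upper end.

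- One event kept, 1/123: the observed risk is 1/123 = 0.8%. The upper limit solves P(X ≤ 1 | n = 123, p) = 0.025, which gives p = 4.4%.
- That woman removed, 0/122: the observed risk is 0%. The upper limit is 1 − 0.025^(1/122) = 3.0%.

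The upper limit falls by about 1.5 percentage points because one woman was left out, although nothing more is known about safety. The arithmetic is nearly the same if the event is in the arm of 122: 1/122 has an upper limit of 4.5% and 0/121 has 3.0%.

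**What it does not do**

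As a test between arms, 1/123 against 0/122 gives a two-sided Fisher p of 1.0, the same as no events at all. The loss shows in the estimate and its interval, not in a significance test.

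**The case against.** The case on the other side has several parts.

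- **The article condenses a fuller protocol, and an analysis plan may define a safety population.** This stands as far as absence goes: one can say only that no set by product received is named in this article. It does not remove the point, because the article states a rule for all outcomes, and a later treated set would have to depart from it.
- **Side effects may not be meant as outcomes.** The relevant section is headed with outcomes and safety measures as separate items and lists side effects after the outcomes. That is a fair reading of that section, but the Objective says the opposite. The two need reconciling.
- **A reader might infer that events are deleted or that harm is necessarily understated.** The documents do not support this. Events remain registered and reportable. Antithrombotic treatment before delivery is a baseline fact, and participants, investigators and statisticians are blinded, so excluding on it could remove a placebo event as readily as a fibrinogen event.
- **A reader might infer that one lost event could flip a significance test.** It could at 6 events against 0 (6/123 against 0/122, p = 0.029; 5/122 against 0/122, p = 0.060). That many events is not a realistic expectation. The only thrombosis rate in the article, 3.48 per 100,000 treatments from surveillance in other settings and with 4 g, gives 123 × 0.0000348 = 0.004 expected events. At an assumed risk of 1%, six or more among 123 has a probability of about 0.0016.
- **Late discovery of ineligibility may be rare.** Women are informed at 29 weeks and asked at the pre-anaesthetic evaluation, so screening is not confined to the acute bleed. The number could be zero.
- **Women given the wrong product:** nothing in the article suggests this is expected. Numbered envelopes and separate dispensing staff make it unlikely, so it is no ground for criticism by itself.
- **Overlap with the efficacy set:** keeping all randomised women in the intention-to-treat set would also bring back a woman later found ineligible. It would still group harms by allocation.

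**Conclusion.** The point holds in a limited form. Read together, the Objective and the statistical section restrict the comparison of harms to eligible women with standing consent. A dosed woman later found ineligible is therefore outside it, and this follows from what the article states rather than from silence.

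The size is unknown because the article does not give the number of such women. It is nil if there are none. If there is one and she has the only thrombosis in her arm, the upper 95% limit moves from 4.4% to 3.0%. This assumes arms of 123 and 122 and one event. No direction of bias is shown. It is a cheap improvement, not a threat to the trial's conclusions.

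**What to change.** In the section on statistical methods, limit the eligibility-restricted set to efficacy outcomes. Then add wording such as: the side effects listed under outcomes and safety measures are analysed in all women who received any amount of trial infusion, grouped by the product actually received, regardless of later-found eligibility or of whether the dose was completed. For women who withdraw, data are used up to withdrawal as consent allows. If a full protocol or analysis plan already defines such a set, the statement about all outcomes should be brought into line with it.

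The cost is one extra population flag and one table. The side effects are already being registered, and sample size, trial conduct and the efficacy analysis are unchanged. The wording should be settled before the allocation code is revealed.
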